### Data analysis

2.8

All data will be analyzed by the researcher using the statistical package for the social sciences (SPSS) 20.0 software, IBM Corporation. If missing data are identified, intention-to-treat will be used to ensure unbiased estimates of treatment effects between the two groups, and all participants who are recruited at baseline will be included in the outcome analysis.^[47]^

The characteristics of the participants will be presented in descriptive statistics. Mixed model ANOVA will be used to evaluate time, group and interaction effects of the interventions on participants’ pain, knee swelling, knee range of motion and quadriceps strength, as well as on the patients’ functional performance and quality of life. Further, multiple regression will be used to determine how much do recovery in physical impairments following low-intensity pulsed ultrasound as an adjunct to conventional physiotherapy influence the functional performance and quality of life of the patients. The level of significance is set as *P* < .05.

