### Assessment of outcomes

2.6

Two days prior to TKA surgery, a researcher will verbally invite potential participants and briefly explain the purpose and procedure of the study before distributing the information sheets to them. At post-operative day 2, the participants will be further screened for eligibility and an informed consent will be obtained from patients who are eligible and agreed to participate. Once recruited, the socio-demography, information of height, weight and body mass index (BMI) of the participants will be recorded. The dose of analgesic medication used will be obtained from patients’ medical record (in-patient) and based on the patients’ report (out-patient).

All participants will undergo baseline assessments before allocated alternately into the two groups at post-operative day 2 for physical impairments, and quality of life following removal of drainage tubes and discontinuation of patient-control analgesia. Baseline assessment for functional performance will be performed at week 1 after the surgery.

Assessment of outcomes following intervention will be conducted at 4 assessment time points which are at week 1, 4, and 12 following TKA surgery and at 3-month follow-up (6 months after the surgery). Outcomes on physical impairments will be assessed at the end of week 1, 4, and 12 following the surgery and at 3-month follow-up. Whereas, outcome on the functional performance will be assessed at week 4 and 12 after the surgery and at 3-month follow-up. Finally, the interventions’ outcome on quality of life of the participants will be assessed at 3-month follow-up or 6-month post-surgery.

A trained physiotherapist who is blinded to the participants’ group allocation is responsible to conduct and record all assessments. To avoid recall bias, the recorded measurements of patient's pre-intervention status will not be accessible to others during the patient's post-intervention assessment.

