### Sample size

2.7

The sample size required for this study will be calculated based on the results of an ongoing pilot study. The pilot study involves 10 subjects per group; a sample size which is considered adequate to assess the effect size in a pilot study of clinical trial.^[46]^ The approximates of parameters, mainly effect size, obtained from the pilot study will then be inputted in G∗Power 3.1. ANOVA repeated measures, within-between interaction statistical test, with the number of groups and measurements 2 and 5 respectively will be used in the calculation. Level of significance is set at an alpha level of 0.05 and a statistical power of 80% will be chosen.

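### Section 2.8 names intention-to-treat as the method for missing data and says that it ensures unbiased estimates; it can do neither, and the promise to include everyone conflicts with the planned ANOVA if that is the classical repeated-measures form

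*Protocol article*

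**What the plan says.** Section 2.8 (Data analysis) makes three statements that have to fit together.

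- The rule for missing data: "If missing data are identified, intention-to-treat will be used to ensure unbiased estimates of treatment effects between the two groups".
- The analysis population: "all participants who are recruited at baseline will be included in the outcome analysis".
- The model: "Mixed model ANOVA will be used to evaluate time, group and interaction effects of the interventions". It covers the four primary impairment outcomes, functional performance and quality of life.

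The software is the "statistical package for the social sciences (SPSS) 20.0 software"; no procedure within it is named. Section 2.7 (Sample size) enters the following in the power program: "ANOVA repeated measures, within-between interaction statistical test, with the number of groups and measurements 2 and 5 respectively".

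Section 2.6 (Assessment of outcomes) fixes the schedule. Impairments have a baseline on post-operative day 2, and then: "Outcomes on physical impairments will be assessed at the end of week 1, 4, and 12 following the surgery and at 3-month follow-up". Functional performance has its baseline at week 1, and then: "outcome on the functional performance will be assessed at week 4 and 12 after the surgery and at 3-month follow-up". Quality of life has a day-2 baseline and one later assessment: "quality of life of the participants will be assessed at 3-month follow-up or 6-month post-surgery".

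**The concern.** The sentence on missing data joins two separate questions. Intention-to-treat answers which participants count and in which arm. What to do when a participant has no week-12 value is another question, and the answer needs a model or an imputation together with an assumption about why the value is missing. Whether the estimate is then unbiased depends on that assumption. The protocol gives the answer to the first question as if it settled the second, and attaches a guarantee.

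The named model makes this more than a matter of terms. In its classical form, a mixed-design ANOVA with time within and group between participants needs a complete set of measurements, and the SPSS repeated-measures procedure excludes anyone without one. If that is what is run, the promise to include everyone fails at the first missed visit, and a complete-case result would be reported as intention-to-treat. Every group comparison in the trial rests on this model.

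**Working it through.** **No figure to reproduce.** The article gives no main-study sample size, effect size or dropout rate. What can be checked is the count of measurements. Day-2 baseline plus weeks 1, 4 and 12 plus the 3-month follow-up makes 1 + 4 = 5, which matches the five measurements in section 2.7. The sizing test therefore fits the impairment outcomes and is a repeated-measures ANOVA.

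**The sentence under each reading of the plan.**

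| Reading of the model | Is everyone included? | What does freedom from bias rest on? |
|---|---|---|
| Classical repeated-measures ANOVA | No, complete cases only | Missingness that does not distort the comparison among completers |
| Likelihood-based linear mixed model | Everyone with at least one value of the outcome | Missing at random |
| Imputation, then ANOVA | Yes | The imputation model |

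In no row does intention-to-treat supply the guarantee.

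**Loss of participants under the classical reading.** Inputs: k follow-up visits from section 2.6 (4 for impairments, 3 for functional performance, 1 for quality of life); a proportion p missing at each visit, which is assumed; baseline taken as complete.

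- If the same people miss every visit, the loss is p.
- If misses are independent between visits, the loss is 1 − (1 − p)^k.

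| p (assumed) | Impairments, k = 4 | Functional performance, k = 3 | Quality of life, k = 1 |
|---|---|---|---|
| 3% | 3% to 1 − 0.97^4 = 11.5% | 3% to 1 − 0.97^3 = 8.7% | 3% |
| 5% | 5% to 1 − 0.95^4 = 18.5% | 5% to 1 − 0.95^3 = 14.3% | 5% |
| 10% | 10% to 1 − 0.90^4 = 34.4% | 10% to 1 − 0.90^3 = 27.1% | 10% |

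**Power under the classical reading (illustration).** Interaction F test with 2 groups and m = 5 measurements, assumed correlation ρ = 0.5 and no departure from sphericity. The noncentrality is N·m·f²/(1 − ρ), with degrees of freedom m − 1 = 4 and (N − 2)(m − 1). For assumed effect sizes f of 0.10, 0.15, 0.20 and 0.25, the smallest even N reaching 80% power is 122, 56, 32 and 22. For f = 0.10 the noncentrality is 122 × 5 × 0.01/0.5 = 12.2. N is then multiplied by the proportion retained.

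| Case | Power over the four effect sizes |
|---|---|
| No missing data | 80-84% |
| p = 5%, same people missing | 78-81% |
| p = 5%, independent misses | 71-74% |
| p = 10%, same people missing | 76-79% |
| p = 10%, independent misses | 60-62% |

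**Bias (simulation on assumed inputs).** Five visits, SD 2, correlation 0.6, true group difference 0, 20,000 per arm. The chance of dropping out before the next visit depends on the last observed value. Differences at the final visit, ultrasound minus control:

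| Dropout mechanism | Completers only | Maximum likelihood, all observed data |
|---|---|---|
| Same in both arms | 0.05 | 0.06 |
| Outcome-related in the control arm only | 0.31 | −0.02 |
| Opposite directions in the two arms | 0.72 | 0.04 |

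Simulation noise is up to about 0.06. The completer analysis goes wrong only where the mechanism differs between arms: by 0.31/2 = 0.16 to 0.72/2 = 0.36 of an SD here. Maximum likelihood does well because dropout was generated to depend only on observed values, which is the missing-at-random condition.

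**The case against.** The strongest defence is that the article never says that incomplete participants will be dropped. It names no SPSS procedure; the same package contains a linear mixed model procedure that keeps partly observed participants, and the phrase mixed model ANOVA could mean that. Section 2.7 describes a sizing calculation, which does not bind the handling of incomplete records. The authors may also use intention-to-treat as shorthand for imputation; the source they cite there is not available to check. The choice of method may stand in a fuller document.

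Most of this stands, and it limits the point. A reader might infer that the all-participant analysis cannot happen, or that anyone missing one visit will certainly be excluded. The documents do not support that: the classical ANOVA is the most natural reading, but it is an inference. Nor do they mention carrying values forward, so that is no charge against the plan. Biased results are not established either. Both arms have the same conventional physiotherapy schedule to week 12 and the same weekly telephone calls. Participants and treating physiotherapists are unblinded, and withdrawal is open at any time (sections 2.4 and 2.9), so dropout that differs by arm is possible but not shown.

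What the defence does not reach is the sentence itself. A fuller document could add a method, but it could not make it true that intention-to-treat handles missing values or ensures unbiased estimates. This is a rule stated wrongly, not detail left for later.

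**Conclusion.** The point holds in two parts of different strength.

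Without condition: section 2.8 is wrong to name intention-to-treat as the remedy for missing data and to claim unbiasedness from it.

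Conditionally: if the planned model is the classical repeated-measures ANOVA, as section 2.7 suggests, it contradicts the promise to include everyone recruited. The loss would then be 3-11%, 5-19% or 10-34% of participants in each impairment analysis at 3%, 5% or 10% missing per visit. It would be smaller for functional performance, and equal to the per-visit rate for quality of life. The missingness rates are assumptions, and the ranges span from the same people missing every visit to independent misses. The power figures also rest on assumed effect sizes and correlation. Bias in the group comparison needs outcome-related dropout that differs between the arms.

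**What to change.** In section 2.8, delete the claim that intention-to-treat handles missing data or ensures unbiased estimates. Replace it with wording such as:

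*All allocated participants are analysed in the group to which they were allocated. Each outcome is analysed with a likelihood-based linear mixed model (SPSS MIXED) with group, visit as a categorical factor and group-by-visit interaction, using every observed value. The analysis is valid if data are missing at random, and a sensitivity analysis examines departures from that assumption.*

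The sensitivity analysis can be simple. The covariance structure and the form of that analysis are for the authors to choose once the sample size is known. The text should also acknowledge that someone with no value at all on an outcome adds nothing to this model. That can occur for functional performance, whose first measurement is at week 1, after allocation.

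The cost is a few sentences and slightly more analysis work, in software already planned. The change should be made before outcome data are examined.

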### Study design and setting

2.1

This is a quasi-experimental assessor-blinded study comparing two approaches of physiotherapy, namely Pulsed ultrasound-added physiotherapy group or control group with the participant's allocation ratio is 1:1. This study will be conducted at orthopedic wards and physiotherapy department in the Universiti Kebangsaan Malaysia Medical Centre, Kuala Lumpur, Malaysia. The flow of the study is shown in Figure 1. The process in this study will be first tested in a pilot study, following which a main study will be conducted.

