### Participants allocation

2.3

A systematic allocation method is used to allocate participants alternately into either pulsed ultrasound-added physiotherapy group or control group. The first participant is allocated to one of the groups at random (sealed envelopes) by a research assistant who is blinded from the intervention groups. Then, the next participant will be allocated to the other, and the process continues.

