### Interventions

2.4

The interventions in this study will be conducted for 12 weeks. The Pulsed ultrasound-added physiotherapy group will receive low-intensity pulsed ultrasound and conventional physiotherapy, while the control group will receive conventional physiotherapy alone. Pulsed ultrasound-added physiotherapy and control groups will receive conventional physiotherapy interventions 4 to 5 times for the first-week post-TKA and 2 to 3 times a week for a further 11 weeks. Besides, the application of low-intensity pulsed ultrasound (4–5 times for the first-week after surgery and 2–3 times a week for a further 2 weeks) in the pulsed ultrasound-added physiotherapy group will be started at post-operative day 2.

The conventional physiotherapy that will be used in this study is based on the therapy program for TKA implemented in the Universiti Kebangsaan Malaysia Medical Centre and also based on evidences which showed that exercise interventions which include stretching, strengthening,^[34]^ and functional exercises provide better outcome in recovery following TKA.^[35–37]^ The rehabilitation program for TKA is shown in Table 1.

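### The functional tests have no pre-treatment value: the stated time-by-group ANOVA lets imbalance into their group effect, and its interaction subtracts any treatment effect already present at week 1

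*Protocol article*

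**What the plan says.** - **Design and allocation (2.1, 2.3).** "This is a quasi-experimental assessor-blinded study comparing two approaches of physiotherapy". "A systematic allocation method is used to allocate participants alternately into either pulsed ultrasound-added physiotherapy group or control group". Only the first placement is random.
- **Start of treatment (2.4).** Low-intensity ultrasound "in the pulsed ultrasound-added physiotherapy group will be started at post-operative day 2", with 4-5 sessions in the first week.
- **Functional tests (2.6).** "Baseline assessment for functional performance will be performed at week 1 after the surgery". After that, "outcome on the functional performance will be assessed at week 4 and 12 after the surgery and at 3-month follow-up". No measured functional value from before surgery or from day 2 is described. Section 2.2 asks only that patients report being able to walk and use stairs.
- **Pre-treatment data (2.6).** Physical impairments and quality of life are measured on day 2, before allocation. After recruitment, "the socio-demography, information of height, weight and body mass index (BMI) of the participants will be recorded".
- **Analysis (2.8).** The recorded patient data have one stated use: "The characteristics of the participants will be presented in descriptive statistics". For the comparison of the groups the section names its model and the effects to be tested: "Mixed model ANOVA will be used to evaluate time, group and interaction effects of the interventions", applied to impairments, functional performance and quality of life. No covariate is named. The multiple regression in 2.8 relates impairment recovery to function and quality of life; it is not an adjusted comparison of the groups.
- **Sizing (2.7).** Within-between interaction, 2 groups, 5 measurements, alpha 0.05, 80% power. The effect size and the number of patients await the pilot.

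**The concern.** An unadjusted comparison is usually defended by randomisation together with a true baseline. The functional outcomes have neither. Alternation does not secure balance, and the timed up and go, stair test and six-minute walk are first measured after ultrasound has started. Section 2.6 itself counts week 1 as an assessment following intervention for the impairments, yet calls the same week the baseline for function.

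Two errors are at stake. A difference between the groups in patient mix could be read as an ultrasound effect, or could hide one. And a real early benefit could be subtracted out because it is already in the reference measurement. These are secondary outcomes, but functional recovery is part of the study's stated objective.

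**Working it through.** The protocol gives no sample size, effect size or SD, so there is no figure of its own to reproduce. All values in steps 1-3 are assumptions chosen to show direction and order of size.

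**Step 1. What each ANOVA term estimates.** Let a standardised pre-treatment covariate differ by δ between groups and act on the outcome with loading β(t) at visit t. Let the true treatment effect be τ(t). The expected group difference at a visit is

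D(t) = τ(t) + δ·β(t).

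The functional visits are week 1, week 4, week 12 and 6 months.

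- Group main effect = mean of D over the four visits.
- Interaction contrast = mean of D over the last three visits − D(week 1) = [mean later τ − τ(week 1)] + δ·[mean later β − β(week 1)].

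**Step 2. Numbers put in.**

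| Case | Group main effect | Interaction contrast |
|---|---|---|
| A. δ = 0.4, β = 0.5 throughout, τ = 0 | 0.4 × 0.5 = 0.20 | 0.4 × (0.5 − 0.5) = 0 |
| B. δ = 0.4, β = 0.2 at week 1 then 0.5, τ = 0 | 0.4 × (0.2 + 3 × 0.5)/4 = 0.17 | 0.4 × (0.5 − 0.2) = 0.12 |
| C. δ = 0, τ = 0.5 from week 1 on | 0.5 | 0.5 − 0.5 = 0 |
| D. δ = 0, τ = 0.25 at week 1 then 0.5 | (0.25 + 3 × 0.5)/4 = 0.44 | 0.5 − 0.25 = 0.25 |

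**Step 3. Simulation of the same cases.** 4,000 trials, 30 per arm, between-patient and residual SD 0.6 each. With loading 0.5 the SD at a visit is √(0.5² + 0.6² + 0.6²) = 0.985, so the units are close to SDs.

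| Case | Main effect, unadjusted → adjusted | Interaction, unadjusted → adjusted |
|---|---|---|
| A, estimate | 0.195 → −0.003 | −0.006 → −0.007 |
| A, standard error | 0.223 → 0.184 | 0.180 → 0.185 |
| B, estimate | 0.165 → −0.005 | 0.117 → −0.003 |
| C, estimate | 0.492 → 0.495 | 0.00 → 0.00 |
| D, estimate | 0.446 → 0.445 | 0.246 → 0.246 |

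Cases A and B: adjustment removes the bias from the main effect, and from the interaction when the covariate changes the course of recovery. In A it improves precision for the main effect but not for the interaction. Cases C and D: adjustment does not bring back the effect that the interaction subtracts. Only a different estimand does. A visit-specific difference D(t) keeps τ(t) whole but also keeps δ·β(t), which is why it needs the covariates.

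**Step 4. Precision of a between-group difference.** Interval width is multiplied by √(1 − R²), where R² is the share of variance explained. For R² = 0.2: √0.8 = 0.894, 11% narrower. For R² = 0.4: √0.6 = 0.775, 23% narrower.

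**Step 5. Degrees of freedom.** Four covariates cost 4 between patients. The covariate-by-visit terms add 4 × (4 − 1) = 12 if week 1 stays in the model as an outcome, or 4 × (3 − 1) = 8 if only the later visits are modelled.

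**The case against.** The strongest reply is that this is a condensed article. It never says that covariates are excluded, describing patient characteristics is routine, and a covariate list usually sits in an analysis plan that is not shown. That stands to this extent: the lack of a covariate list is not by itself a finding. But the article does fix when the functional baseline is taken and which effects the model tests, and those two choices produce the problem.

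The second reply is that the trial is sized on the interaction, where stable differences in sex, age or body size cancel. This also stands. A reader might infer that any imbalance passes straight into every result. The documents do not support that: case A shows no bias in the interaction, which is biased only by factors that alter the rate of recovery (case B).

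Two further inferences are tempting and should not be drawn:

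- **That adjustment would lift the planned 80% power to 88%, 92% or 95%** (R² of 0.2, 0.3, 0.4, from 2.80/√(1 − R²)). Those values belong to a single between-group comparison. The 80% in section 2.7 belongs to the interaction, where the simulated standard error did not improve.
- **That chance imbalance shows harm from alternation.** With 25 per arm and 70% women (assumed), the SD of the difference in the share of women is √(2 × 0.7 × 0.3/25) = 0.130, so a gap of 15 points or more has probability 0.25. That would be equally true under randomisation. The harm specific to alternation is selection through a predictable sequence, and the documents give no means of sizing it.

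The no-baseline argument also does not reach quadriceps strength or the other primary outcomes, which have a day-2 value.

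**Conclusion.** The point holds for the functional outcomes in limited form. Their reference measurement follows the start of ultrasound, and the stated model has only time and group. The group effect therefore carries covariate imbalance (about 0.2 under δ = 0.4 and loading 0.5) and loses precision. The interaction escapes time-constant covariate effects, but not those that change recovery (0.12 in case B), and it loses whatever treatment effect exists at week 1: all of a constant 0.5, half of one that rises from 0.25 to 0.5.

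The direction of these results follows from the schedule and the model; the sizes rest on the assumed imbalance, loadings and effects. Two limits apply to the covariates. Section 2.6 says socio-demography without naming age or sex, although age must be known because it is an inclusion criterion. Recording before allocation is explicit only for impairments and quality of life, but age, sex and height cannot be changed by treatment. The change should be made before outcome data are seen.

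**What to change.** In section 2.8:

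1. State that the week-1 functional tests are a post-treatment outcome, not a baseline, and bring section 2.6 into line.
2. For each functional outcome, take as the result the group differences at weeks 4 and 12 and at 6 months from a repeated-measures model adjusted for named pre-treatment covariates: age, sex, BMI and day-2 quadriceps strength, each with a covariate-by-visit term. Report the unadjusted ANOVA as a sensitivity analysis.
3. For the primary impairment outcomes, adjust for the day-2 value of the outcome; age, sex and BMI are optional.
4. State that adjustment addresses measured imbalance only.

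No new measurement is needed, provided that sex is among the socio-demographic items. The costs are the degrees of freedom in step 5, which matter if the main study is small; three visit-specific comparisons per functional outcome; and an estimand that differs from the interaction used for sizing in section 2.7. The text should say so openly, and should claim the precision gain only for the between-group differences.

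### The primary-outcome ANOVA counts the pre-allocation day-2 value as one of five time levels, which dilutes its group effect and leaves no sized, dated treatment difference as the result

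*Protocol article*

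**What the plan says.** The Data analysis section (2.8) fixes the method: "Mixed model ANOVA will be used to evaluate time, group and interaction effects of the interventions", applied to pain, swelling, knee motion and quadriceps strength, and also to functional performance and quality of life. The Sample size section (2.7) plans on the same model: "ANOVA repeated measures, within-between interaction statistical test, with the number of groups and measurements 2 and 5 respectively".

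The visit schedule is in Assessment of outcomes (2.6). For the baseline: "All participants will undergo baseline assessments before allocated alternately into the two groups at post-operative day 2 for physical impairments". For follow-up: "Assessment of outcomes following intervention will be conducted at 4 assessment time points", and for the primary outcomes "Outcomes on physical impairments will be assessed at the end of week 1, 4, and 12 following the surgery" and again at the 3-month follow-up, which is 6 months after surgery. Under Interventions (2.4), ultrasound "will be started at post-operative day 2".

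Section 2.8 names no baseline covariate. It lists time, group and interaction together as effects of the interventions.

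**The concern.** The three ANOVA terms are not equally informative about ultrasound.

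- **Group effect.** With the pre-allocation value as a time level, it is an average over five visits, one of which cannot carry a treatment effect. It understates any true difference and absorbs any difference already present on day 2. Under Participants allocation (2.3) only the first participant is placed at random and the rest alternate, so baseline balance is less assured than under full randomisation.
- **Interaction.** It asks whether the two five-point profiles are parallel. A significant result does not say which group did better, by how much or when.
- **Time effect.** Patients in both groups recover from surgery, so it says nothing about the added treatment.

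At stake is whether the trial ends with an estimate a clinician can use. The Introduction stresses acute pain and swelling, and ultrasound is given only in the first three weeks, so the timing of any benefit matters.

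**Working it through.** **1. Does the day-2 value enter as a level?** Primary outcomes: 1 baseline (day 2) + 4 follow-ups (weeks 1, 4, 12 and 6 months) = 5. This matches the five measurements in section 2.7, and the follow-ups alone give only 4. The count is specific to the physical impairments. Functional performance has 4 measurements (week 1 as baseline, then weeks 4, 12 and 6 months). Quality of life has 2 ("outcome on quality of life of the participants will be assessed at 3-month follow-up or 6-month post-surgery", plus baseline).

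**2. Dilution of the group effect.** It estimates the mean of the five visit differences, with the day-2 difference expected to be 0. No correlation or sample size is needed.

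- Sustained 0.5 SD: (0 + 4 × 0.5)/5 = 0.4 SD.
- Weeks 1 and 4 only: (0 + 0.5 + 0.5 + 0 + 0)/5 = 0.2 SD.

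**3. Day-2 imbalance.** An imbalance of b contributes b/5 through the day-2 level. If each follow-up correlates ρ with baseline (equal SDs), it also carries ρb into each of four visits, for a total of b(1 + 4ρ)/5. At ρ = 0.5 that is 0.6b.

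**4. Precision from adjusting.** With SD 1, the residual variance at one visit is 1 − ρ² adjusted, 2(1 − ρ) for change from baseline, and 1 unadjusted. At ρ = 0.5 these are 0.75, 1 and 1, so adjustment cuts variance by 25%.

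**5. Illustrative power.** The protocol gives no N, effect size, SD or correlation. Assumed: 40 per arm, SD 1, equal correlation between visits, no day-2 difference, two-sided 0.05.

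- Interaction: noncentral F, λ = (n/2)·Σ(d_j − d̄)²/(1 − ρ), df 4 and 4(2n − 2) = 312. At ρ = 0.5, sustained: Σ = 0.16 + 4 × 0.01 = 0.20, so λ = 20 × 0.20/0.5 = 8. Fading (0.5, 0.5, 0.25, 0): Σ = 0.25, λ = 10. Weeks 1 and 4 only: Σ = 0.30, λ = 12.
- Group effect: noncentral t on the five-visit mean, variance (1 + 4ρ)/5. At ρ = 0.5, sustained: 0.4/√(2 × 0.6/40) = 2.31.
- Adjusted week 4: noncentral t, variance 1 − ρ², df 2n − 3. At ρ = 0.5: 0.5/√(2 × 0.75/40) = 2.58.

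| True effect | ρ | Group effect | Interaction | Adjusted week 4 |
|---|---|---|---|---|
| Sustained | 0.3 | 76% | 44% | 64% |
| Sustained | 0.5 | 63% | 60% | 72% |
| Sustained | 0.7 | 53% | 84% | 87% |
| Fading | 0.3 | 38% | 54% | 64% |
| Fading | 0.5 | 30% | 71% | 72% |
| Fading | 0.7 | 24% | 92% | 87% |
| Weeks 1 and 4 only | 0.3 | 27% | 63% | 64% |
| Weeks 1 and 4 only | 0.5 | 21% | 80% | 72% |
| Weeks 1 and 4 only | 0.7 | 17% | 96% | 87% |

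The group effect is weak whenever the benefit is early. The interaction is sometimes behind the single-visit comparison and sometimes ahead.

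**6. Early-visit average.** The adjusted mean of weeks 1 and 4 has variance (1 + ρ)/2 − ρ², which is 0.5 at ρ = 0.5. With 0.5 SD at both visits: 0.5/√(2 × 0.5/40) = 3.16, power 88%. If the effect is late (0, 0.25, 0.5, 0.5), the same contrast averages 0.125 SD and has 12% power, against 71% for the interaction.

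**The case against.** The strongest defence is that the trial is sized on the interaction, not the group effect. The interaction compares change profiles, so the day-2 level serves as its reference and does not dilute it. The stated objective is recovery out to 6 months, for which a test of differing profiles is a recognised choice. Visit-specific contrasts and confidence intervals may sit in an analysis plan not shown, and section 2.8 does not exclude them.

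Most of this stands. The missing contrasts are not in themselves the fault. What remains is what the article does fix: it presents the group and time effects as effects of the interventions, and it ties the sample size to an omnibus test that cannot size or date a benefit.

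A reader might infer two stronger claims, and neither is supported.

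- **That the plan loses power in general.** The table shows otherwise: 80% for the interaction against 72% for adjusted week 4 when the effect is at weeks 1 and 4 only (ρ = 0.5), and near parity, 71% against 72%, when it fades. The 88% for an early average requires knowing the timing in advance.
- **That departures from sphericity inflate type I error.** This presumes a test run without correction. The article does not say so, and such corrections are ordinary analysis-plan detail.

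**Conclusion.** The point holds as a matter of efficiency and interpretability. It does not make the planned test invalid. For the four physical impairments, the day-2 value is one of the five levels. The group effect is therefore diluted to four fifths of a sustained difference, and to two fifths of one confined to weeks 1 and 4. It is also exposed to day-2 imbalance. The interaction is valid but does not supply direction, size or timing, and the time effect is not evidence for ultrasound.

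The dilution factors rest only on the visit count and on no treatment effect before allocation. The power figures are illustrative: 40 per arm, 0.5 SD and ρ from 0.3 to 0.7 are assumptions, none of them from the protocol.

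**What to change.** In section 2.8, analyse each primary outcome with a model for the four post-baseline visits (weeks 1, 4, 12 and 6 months), containing group, visit, group-by-visit, day-2 baseline and baseline-by-visit. Take as the primary result the adjusted group difference with its 95% CI at one visit, or over an early-visit average, named in advance. Report the other visits from the same model. State that neither the time effect nor a group effect that includes baseline will be used as evidence of efficacy.

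In section 2.7, base the sample size, which is still to be calculated, on that same contrast in place of the five-measurement interaction.

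Cost: both sections change, but no new data or visits are needed because the day-2 value is already collected. The real price is committing to a contrast, which loses power if the effect falls at other visits (12% in the late-effect example). Adjustment deals with measured day-2 differences only and does not repair other weaknesses of alternate allocation.
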